### Settings and target population

Municipalities located in the north, middle and south-eastern part of Norway will be contacted to participate in the trial. To ensure collaboration and implementation throughout the trial, we will arrange meetings with the health care leaders in the municipalities and the managers and physicians working in each nursing home. We will strive to recruit nursing homes located in both rural and urban areas of Norway and to obtain an equal distribution of large and small nursing homes to ensure a representative nursing home population. Nursing homes already using TIME as part of their clinical routines will not be invited to take part in the trial.

All patients in wards in participating nursing homes will be considered eligible for inclusion in the trial, and will be assessed to determine if they meet the inclusion criteria. Trained nursing home staff will perform the assessments. The research team will train these staff members on the inclusion procedure and the assessment of patients’ capacity to provide consent. The data obtained from screening individual eligible patients will not be recorded. Patients who fulfil the inclusion criteria and agree to participate will be included in the trial. For patients who lack the capacity to provide consent, written consent will be obtained from their next of kin.

The inclusion criteria for patients are as follows:NH patients with probable dementia, defined as a Clinical Dementia Rating scale (CDR) [16] score of one or higher.A moderate to high degree of agitation, defined by an NPI-NH agitation item score equal to or above six points.Long-term patients who have resided in the nursing home for a minimum of two weeks before inclusion.

The exclusion criterion for patients is a life expectancy of less than 4–6 weeks.

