### Sample size calculation based on the primary outcome

The primary outcome of the trial is the change in the level of agitation from baseline at eight weeks, as measured by the agitation item of the Neuropsychiatric Inventory-Nursing Home Version (NPI-NH) [17, 18]. Power calculation was based on the following assumptions. A previous non-controlled pilot study of TIME showed that the intervention decreased the NPI-NH agitation item score by on average 2.8, with a standard deviation (SD) for change of 3.1 [13]. One can reasonably assume that the simple education-only intervention and baseline and follow-up assessments may have some effect on the control group. Therefore, we expect that the difference in the effect between the control and intervention groups will be lower. We have assumed a mean difference between the groups to be 1.5 as measured by NPI-NH agitation item, and that this difference will have a SD of 3.1. Based on this assumption, we calculate that 65 persons must be included in each group to observe a statistically significant difference with a power of 80 % and a significance level of 5 %. We assume an intra-cluster (nursing home) correlation coefficient (ICC) of 0.05. The ICC is assumed to be low because the persons included will be located in different departments and units in the nursing home (the cluster). Adjusting power calculations for cluster effect, we find that at least 78 persons have to be included in the intervention group and 78 in the control group for the effect to be statistically significant. That is, we need a total of 156 persons. Based on previous studies, we assume that the average size of the nursing homes is 46 patients and that each nursing home will recruit five patients, on average. In the pilot study, we found that approximately 12 % of patients had dementia and an NPI-NH agitation item score of six or higher, which is our main criterion for inclusion. Previous studies have shown that we can anticipate a 30 % loss to follow-up per year (due to, e.g., mortality, relocation, or withdrawal from the study)—that is, 7.5 % in three months. Thus, we will need a total of 168 people (84 persons in each group), indicating that we will need to screen approximately 1400 nursing home patients. Given approximately 46 patients on average per nursing home, we will need to recruit approximately 30 nursing homes. The nursing homes will be randomized after the baseline assessment to avoid bias. The recruitment of new patients to the study will therefore occur only through the recruitment and randomization of new nursing homes, as described above.

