### Procedures for data collection

The patients’ demographic data, baseline data and primary and secondary outcomes will be collected by project nurses not affiliated with the nursing homes. All 10 assessors are nurses with substantial experience and formal training on the use of the assessment scales. They attended a one-day course on the use of the assessments scales before start of the trial. The assessments of all outcomes and covariates will be repeated at 8 and 12 weeks after baseline. The assessors will collect the data via telephone by interviewing staff members who know the patient best. The assessors will be blinded to the randomization of the nursing homes. The following data from patients’ medical records will be collected: age, gender, marital status, type of ward the patient lives in (regular somatic, special care units for dementia patients or other types), known diagnoses (chronic diseases), and dementia diagnosis.

The following data describing the nursing homes will be assessed by a questionnaire sent to the leading ward registered nurse at the start of the trial: the size of the nursing home (number of patients); the size of the unit and ward (the number of patients per unit and ward); the care factor (the number of nurses working per patient per work shift); the number of hours the nursing home physician works per patient per week in the nursing home/unit; and the number of employees per leading ward registered nurse.

Covariates that will be measured are: level of dementia, as assessed by the CDR; level of functioning in daily activities, as measured by the Physical Self-Maintenance Scale (PSMS; [21]; and physical health, as measured by the General Medical Health Rating Scale (GMHR; [22]. PSMS is a six-item scale that produces a sum score ranging from 6 to 30. A higher score denotes more severe functional impairment. GMHR is a one-item global rating scale with the categories good, fairly good, poor and very poor.

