### Data processing and statistical analysis of quantitative data

All data regarding the cluster randomized trial will be collected via telephone. The data will be registered online in the dataset prepared for the study using the data tool Checkbox via a web survey to the SQL database. The questionnaires used to collect all other data will be distributed to staff (regardless of job position) by mail and the results will be stored in the same manner as the trial data. At the 6- and 12-month assessments, questionnaires will be sent only to the staff who responded to the previous questionnaires.

The data will be presented as frequencies and percentages for categorical and means (standard deviations) for the continuous variables. The normality of continuous variables will be assessed graphically. If necessary, skewed data will be transformed. Differences in the changes in outcomes between the intervention group and the control group will be assessed by a linear mixed model with fixed effects for time component and group and the interaction between the two. A significant interaction will imply the differences in change between the groups. Random effects for patients nested within nursing homes and slopes (if significant) will be included into the model. Individual time point contrasts will be derived within each group at each time point with the corresponding 95 % confidence intervals and *p*-values. Linear mixed model correctly adjusts estimates for intra-cluster correlations as well as for intra-individual correlations due to repeated measurements in time. The model also handles unbalanced data by allowing inclusion of all available information, also from drop-outs.

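### The stated patient random intercept, with a slope only if significant, can misstate the week-8 standard error in either direction, so the claim that it adjusts correctly is not assured

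*Protocol article*

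**What the plan says.** The section on data processing and statistical analysis specifies a linear mixed model with time, group and their interaction. The dependence structure is given in one sentence: "Random effects for patients nested within nursing homes and slopes (if significant) will be included into the model". The article then states: "Linear mixed model correctly adjusts estimates for intra-cluster correlations as well as for intra-individual correlations due to repeated measurements in time". It names no residual covariance, does not say whether time is coded as visits or as weeks, and does not say what form a slope would take.

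The visit schedule is under Procedures for data collection: "The assessments of all outcomes and covariates will be repeated at 8 and 12 weeks after baseline". The primary outcome is the between-group difference in change at week 8 on the NPI-NH agitation item, scored 0 to 12. Entry depends on the same item: "A moderate to high degree of agitation, defined by an NPI-NH agitation item score equal to or above six points".

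The sample size section gives the only variability figure, taken from the pilot: "with a standard deviation (SD) for change of 3.1". No SD at any single visit and no correlation between visits is given.

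**The concern.** A mixed model gives a correct SE for a contrast between visits only if its covariance can represent the data. A patient random intercept with independent residuals forces the same variance at every visit and the same correlation between every pair of visits. Here the visits are unequally spaced. Weeks 8 and 12 are 4 weeks apart, baseline and week 8 are 8 weeks apart, and baseline is the visit closest to selection. It is plausible that the two follow-up ratings are the most alike.

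Under a random intercept the model uses one change variance for all three pairs of visits. A small week 8-to-12 change variance would then pull down the SE of the primary baseline-to-week-8 contrast, and a large one would push it up. A slope linear in weeks relaxes this only partly, because it cannot represent a single step in variance after baseline followed by a plateau.

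At stake are the width of the primary confidence interval and the true level of the test. This is a patient-level matter: it remains with no nursing-home effect at all, and modelling the home effect well does not remove it.

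**Working it through.** **Inputs from the article.** SD of change 3.1, so variance 9.61; visits at 0, 8 and 12 weeks; 78 per group after the cluster adjustment.

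**Assumed inputs.** Baseline SD 2.0; SD 3.1 at weeks 8 and 12; baseline-to-follow-up covariance 2.0, which is a correlation of 2.0/(2.0 × 3.1) = 0.32; complete data; independent residuals; any slope linear in weeks; no home effect. These reproduce the article's SD of change: 4.00 + 9.61 − 2 × 2.00 = 9.61 = 3.1².

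**The article's own figure.** It reports that "we calculate that 65 persons must be included in each group", "with a power of 80 % and a significance level of 5" per cent, for a difference of 1.5. The usual two-sided formula gives 2 × (1.960 + 0.842)² × 9.61 / 1.5² = 67.05, so 68 per group; 65 per group gives 78.8% power. Nothing below depends on this small gap.

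**Random intercept only.** With balanced data the model variance of any change is the mean of the three pairwise change variances:

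model variance = [Var(0,8) + Var(0,12) + Var(8,12)] / 3, with Var(8,12) = 2 × 9.61 × (1 − ρ) and ρ the week 8–12 correlation.

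SE ratio = √(model variance / 9.61). Type I error = P(|Z| > 1.96 × SE ratio).

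Example, ρ = 0.7: Var(8,12) = 5.77; mean = (9.61 + 9.61 + 5.77)/3 = 8.33; ratio = √(8.33/9.61) = 0.931; type I error 6.8%. The model is exact when 19.22 × (1 − ρ) = 9.61, that is at ρ = 0.5.

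**With a linear slope.** Fitted by maximum likelihood to the same 3x3 matrices.

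| Week 8–12 correlation | Intercept only: SE ratio, type I | With slope: SE ratio, type I |
|---|---|---|
| 0.32 (all equal) | 1.057, 3.8% | 1.045, 4.1% |
| 0.5 | 1.00, 5.0% | 0.986, 5.3% |
| 0.6 | 0.966, 5.8% | 0.952, 6.2% |
| 0.7 | 0.931, 6.8% | 0.915, 7.3% |
| 0.8 | 0.894, 8.0% | 0.869, 8.9% |

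In the rows from 0.5 to 0.8, the likelihood ratio for the slope at 156 patients is 33 to 83. The significance rule would keep the slope, and there it gives the smaller SE.

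**Scale.** Before any cluster inflation, the correct SE with 78 per group is 3.1 × √(2/78) = 0.496. At a ratio of 0.915 the model would report 0.496 × 0.915 = 0.454, a 95% half-width of 0.89 instead of 0.97.

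**Wider assumptions.** SD of change was held at 3.1, baseline SD varied over 1.5–2.3, the baseline–week 8 correlation over 0.2–0.5, and the week 8–12 correlation over 0.4–0.8, giving 60 combinations. The SE ratio runs from 0.88 to 1.11 with the intercept alone (type I error 8.6% to 3.0%) and from 0.84 to 1.09 with the slope (9.8% to 3.2%). The SE is too small in 43 of the 60 with the slope and about 38 without. That count describes the grid chosen and is not a probability.

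**Simulated 0–12 item scores with selection at 6 or more.** Where correlation decays with time, the slope model's ratio is 0.93–0.98 (type I error 5.4–6.8%) in all 16 settings, whether recorded baseline is the screening score or a re-rating. Where correlation is the same at all intervals, the ratio is 1.00–1.01 with the slope and 1.00–1.04 without.

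**Is the cut-off the cause?** The 0.32 row has a variance step after baseline and no extra week 8–12 correlation; its SE is too large. Now remove the step by setting every SD to 2.66, which keeps the change variance: 2 × 2.66² × (1 − 0.32) = 9.62. With a week 8–12 correlation of 0.7 the ratios are 0.902 and 0.879, lower than the 0.931 and 0.915 with the step. The step therefore offsets part of the shrinkage; the week 8–12 correlation produces it.

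**The case against.** The strongest reply is that the article does not fully specify the model criticised here. Independent residuals and a slope linear in weeks are my reading. A condensed article may leave residual structure and time coding to an analysis plan, and naming patient random effects does not exclude a visit-specific residual covariance. The sentence about correct adjustment can also be read as a general reason for using mixed models. This stands as a limit: the point is conditional on that reading. It does not dispose of the point, because the article does fix the patient random effects and a significance rule for slopes, and attaches an unqualified assurance to them.

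The second reply is that the result turns on correlations the article does not give. That is right. With the assumed SDs, a week 8–12 correlation of 0.4 gives a type I error of 4.3% (intercept) or 4.6% (slope), which is conservative.

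A reader might infer something stronger: that because entry requires a score of 6 or more, recorded baseline can take only the values from 6 upwards, variance must rise afterwards, and the week-8 SE is therefore usually too small. The article does not support this. Nursing-home staff do the screening and those data are not recorded, while outside project nurses rate baseline; nothing says the recorded baseline is the screening score or that re-rated values below 6 are excluded. Even with truncation, the variance step works against the shrinkage, as shown above.

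**Conclusion.** The point holds in a conditional form. Under the usual reading, the stated patient-level covariance can misstate the SE of the primary week-8 contrast in either direction, so correct adjustment for within-patient correlation is not assured.

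If the closer ratings at weeks 8 and 12 are the more highly correlated, the SE is likely too small. In the main set of assumptions the slope model's SE is about 1% to 13% too small, with type I error of about 5.3% to 8.9%, for week 8–12 correlations from 0.5 to 0.8. If all correlations equal 0.32, the SE is 4–6% too large and the error about 4%. The effect is modest in most settings.

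A flat statement that the interval is too narrow, or that the test exceeds 5%, would go beyond the documents. All visit SDs and correlations used here are assumptions, apart from the constraint that the SD of change is 3.1.

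**What to change.** - Treat visit as a three-level factor (baseline, week 8, week 12) with an unstructured 3x3 within-patient covariance, in place of the patient random intercept and slope.
- Keep the nursing-home effect as a separate term. Whether that term should vary over time is a different question.
- Take the between-group week-8 contrast and its SE from this model.
- Drop the significance test for patient slopes, which makes the primary model depend on the data.
- Reword the sentence on correct adjustment, for example to say that the model allows for correlation within homes and within patients through the stated covariance.

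The cost is a few lines of analysis wording and a standard software option. Six covariance parameters are easily estimated from about 168 patients. The interval may become slightly wider. In return, the patient-level SE no longer depends on assumed equal or linear-in-time correlation. If a full analysis plan already specifies such a residual structure, only the article's wording needs aligning with it.

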### Trial status

The cluster randomized trial will be carried out from January to the end of June 2016.

Focus groups will be held in September and October 2016. The part of the trial evaluating the implementation process started in December 2015 and continue until the end of April 2017.

## Discussion

The main purpose of this trial is to improve the assessment and treatment of agitation in persons with dementia by examining the effect and implementation of the TIME intervention model. The strength of the model is that it was developed in nursing homes over a period of several years; thus, it takes into account the nursing home context. A pilot study showed its feasibility and further developed the model [13]. The model integrates pharmacological and nonpharmacological treatments for use in real-world implementation. The components of the model have a solid theoretical foundation [6, 20, 35]. Given that NPS often represent complex problems with multifactorial causes that interact with each other, often in unpredictable ways, multifaceted and complex interventions must be applied.

One of the challenges of psychosocial interventions is effectively and sustainably implementing them. Fixsen defined implementation as a specific set of activities combined in practice to introduce an activity or a programme with known components. Similar to an actual intervention (programme or model), implementation includes a set of activities and a set of outcomes [36]. Richards and Hallberg defined complex interventions as “Activities that include multiple components with the potential for interactions between them. When such an intervention is applied to the target population a number of possible and varied results are created” [37]. Based on this description, we claim that TIME satisfies the definition of a complex intervention [14]. An intervention’s complexity must also be considered based on the context—that is, the type of organization and the organization’s various participants [38]. A lack of an effect may reflect the failure of implementation rather than shortcomings of the implemented programme or model [38]. Therefore, the implementation of complex interventions is particularly demanding.

The Medical Research Council (MRC) defines an overarching framework for the development and evaluation of complex interventions. This recommendation was revised in 2008 to place greater emphasis on the importance of the process evaluation and adaptation to local contextual conditions compared with the previous recommendations [39]. In our trial, we will follow these recommendations and simultaneously apply an experimental design for measurements of effectiveness at the patient level and conduct an experimental evaluation of the implementation. Our reports on the TIME trial will follow the recommendations presented in the CONSORT 2010 statement: extension to cluster randomized trials [40].

A design that combines clinical effectiveness and implementation outcomes in one trial is called an effectiveness-implementation hybrid design [41, 42]. The main advantage of this hybrid design is that it can accelerate the translation of research findings into routine practice. It also allows the research team to evaluate the results regarding effectiveness in light of the degree of fidelity and adoption of the model. For this advantage to be realized, the implementation strategies in the trial cannot be overly complex. Thus the implementation strategies should not demand basic structural changes within the organization receiving the intervention. Although TIME is a complex intervention, we experienced during the pilot study that the intervention does not require significant changes within the organizations’ structures or routines, and the implementation costs were estimated to be low.

Our study design has some limitations. We do not require a precise diagnosis of dementia as an inclusion criterion; instead, we include patients with probable dementia, defined as a CDR score of one or higher. A previous study on a Norwegian NH showed that only approximately one-third to one-half of residents with dementia were assessed and given a diagnosis of dementia [1, 43]. In addition, several studies have shown that CDR staging based solely on an informant interview is a valid substitute for patient examinations [43, 44]. Therefore, even if a few patients included in our study do not fulfil all the criteria for a dementia diagnosis, the use of the CDR as a criterion for inclusion instead of a precise diagnosis of dementia will strengthen the external validity of our findings. Another limitation is the rather short follow-up time. The last visit in which the patient outcomes will be assessed is the 12-week visit, primarily due to resource limitations and to ensure staff compliance. To be considered clinically important, an intervention aimed at reducing NPS should show some measurable effects after 8 to 12 weeks. The data collection concerning the implementation process will nevertheless span a year to measure the sustainability of the intervention.

## Conclusion

The increasing percentage of the population with dementia will be a major challenge for health and care facilities in the coming years. Nearly all people who suffer from dementia experience NPS in the course of their disease. NPS like agitation, including physical or verbal aggression and excessive motor activity cause patients to experience profound suffering and a reduced quality of life and caregivers to suffer increased burden [4]. TIME is a multicomponent intervention based on the theoretical framework of CBT. The TIME trial is an effectiveness-implementation cluster randomized trial designed to assess both effects on NPS in persons with dementia residing in nursing homes and the implementation process at the staff and organization levels. An open pilot study conducted in 2010 showed that the intervention is feasible and found a reduction in patients’ agitation and mood symptoms and caregiver strain. The trial will take place in 30 nursing homes and will include 168 patients with dementia and a high degree of agitation. The aim of this project is to make an important contribution to improve the treatment of NPS. Furthermore, the project may result in an evidence-based model for assessment and treatment in both primary care and specialist care. The project will provide additional insight into how to sustainably implement complex interventions.

